### Sample size calculation

The sample size estimate has been made assuming a power of 80%, a confidence level of 95% in order to detect a standardized significant difference of at least 0.5. We consider 0.5 to be a clinically relevant difference based on the article by Norman et al. [20], being 128, the minimum sample size needed to detect this difference, 64 people in each group. A 10% sample size is added to compensate possible losses or errors in the follow-up, which represents 140 patients.

### Randomization

Subjects’ allocation to the two groups will be carried out by simple random sampling stratified by hospital. This sampling will be processed by a computer program that randomizes the patients in each hospital. Randomization will result in two lists of random numbers between 1 and 50 in each hospital. In each research center there will be 50 opaque and sealed envelopes numbered from 1 to 50. Each envelope will contain the group for that particular patient (intervention vs. control). The number on each envelope will correspond with the entry order number of each subject and will be opened once the patient has been included in the study. Each hospital must recruit a minimum of 20 patients and a maximum of 50 patients. Recruitment will end when sample size is reached.

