### Limitations of the study

Even if the ACP program intervention is homogeneous in both groups, and everyday clinical practice is very similar in all centers, the organization of each HF Unit can vary. Despite this fact, this scenario parallels real clinical variability. Even though clinical management will be similar in both groups, as an open clinical trial there is a risk of expectation and attention bias. This might make it difficult to ensure that researchers' higher engagement with patients in the intervention group will not skew results. Finally, the study is restricted to patients with advanced HF, and therefore its conclusions and extrapolation to other advanced chronic pathologies is limited.

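### Simple randomisation within each hospital does not secure arm balance within hospitals, so the stated stratification achieves little; the cost in validity and power is small and the repair is cheap

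*Protocol article*

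**What the plan says.** The Randomization section of the protocol article states that allocation "will be carried out by simple random sampling stratified by hospital". A computer program produces the sequence for each site, and "Randomization will result in two lists of random numbers between 1 and 50 in each hospital". The mechanics follow: "In each research center there will be 50 opaque and sealed envelopes numbered from 1 to 50", and "The number on each envelope will correspond with the entry order number of each subject". A site therefore uses its envelopes in order and opens only as many as it recruits.

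Site size is bounded: "Each hospital must recruit a minimum of 20 patients and a maximum of 50 patients". The total is bounded too: "Recruitment will end when sample size is reached". The sample size section sets that total at 140, allowing for losses on top of 128 (64 per group). The section names no block or other restriction, and does not say whether the two lists are of equal length.

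Under Limitations of the study, the article calls the trial open. It describes everyday practice as much alike across centres, but adds that "the organization of each HF Unit can vary".

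**The concern.** The usual purpose of stratifying by hospital is to give each hospital similar numbers in the two arms, so that differences between hospitals do not fall unevenly on the comparison. That takes a restriction within each hospital, such as blocks. Independent coin-tosses run separately in four hospitals have the same distribution as coin-tosses run once over all patients. On its plain wording, the method carries the label of stratification without its effect.

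The two-lists sentence allows a second reading: the numbers 1 to 50 are divided 25/25 between the arms. That is a single block of 50 per hospital. It restricts allocation, but guarantees equal arms only when the list is finished, and the recruitment rules prevent most sites from finishing it.

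At stake is chance imbalance in a factor that may be related to outcome, because the control arm receives each unit's usual follow-up. This is a matter of precision and face validity, not of the validity of the test.

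**Working it through.** **Inputs.** From the Randomization section: simple randomisation, 50 envelopes per site in entry order, 20 to 50 patients per site. From the sample size section: standardised difference 0.5, power 80%, confidence 95%, 64 per group, 140 in total. From the design section: four hospitals. Assumptions: two-sided 5% test, and 35 patients per hospital (140 / 4) as the even case.

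**The plan's own figure.** A two-sided t-test at d = 0.5 needs 63.77, so 64 per group, with power 80.1%. This reproduces 128. Adding 10% gives 128 × 1.1 = 140.8, against the stated 140.

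**How many lists can be finished.** Envelopes: 4 × 50 = 200. Unopened at the end: 200 − 140 = 60. Three full sites would need 150 patients, more than 140. Two full sites leave 140 − 100 = 40, exactly 20 + 20. So at most two sites can finish, and at least two lists are cut short.

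**Spread of the arm difference in one hospital of n patients.**
- Simple randomisation: SD = √n. n = 20: 4.5; n = 35: 5.9; n = 50: 7.1.
- 25/25 list cut at n: SD = √(n(50 − n)/49). n = 20: √(600/49) = 3.5; n = 35: √(525/49) = 3.3; n = 50: 0.

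**Chance of a marked split.** X is the number in one arm: Binomial(n, 0.5) for simple randomisation, Hypergeometric(50, 25, n) for a 25/25 list. By symmetry the two-sided chance is twice the upper tail.

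| Event | Simple | 25/25 list |
|---|---|---|
| n = 20, 13:7 or worse: 2·P(X ≥ 13) | 0.263 | 0.148 |
| n = 35, 22:13 or worse: 2·P(X ≥ 22) | 0.1755 | 0.0121 |
| At least one of four hospitals of 35 | 1 − (1 − 0.1755)⁴ = 0.54 | 1 − (1 − 0.0121)⁴ = 0.048 |

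**What it costs in power.** Over 140 patients, simple randomisation gives an arm difference with SD 11.8 and 95th percentile 24, that is 58 against 82. Unadjusted t-test power at d = 0.5, before losses:

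| Split of 140 | Power |
|---|---|
| 70/70 | 83.6% |
| 63/77 | 83.2% |
| 58/82 | 82.5% |

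The loss at the 95th percentile is 83.6 − 82.5 = 1.1 points.

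**With blocks.** Within a block the arm difference cannot exceed half the block size. Blocks of 4 and 6 therefore hold it to at most 3 in any hospital, wherever recruitment stops.

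**The case against.** The strongest reply is that little harm follows. Allocation uses opaque, sealed, numbered envelopes opened after inclusion, so any hospital imbalance is chance. It neither biases the comparison nor inflates the type I error. This stands in full. A reader might infer from the remark on differing HF units that hospital is a likely confounder. The documents do not support that: the same sentence describes practice as very similar across centres, and no between-hospital difference in PAM is given. Hospital is at most a prognostic factor that may be unbalanced by chance.

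A reader might also infer that because an arm can be randomised at 63 or fewer, the planned 64 per group and the 80% power are lost. That does not follow, since power depends on both arm sizes and 63/77 of 140 still gives 83.2% before losses.

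The larger figures belong to the plainer reading of an ambiguous section. Under 25/25 lists the 54% becomes about 5%. This is correct, and both sets are shown for that reason. Even then the short lists leave a 15% chance of 13:7 or worse at a site of 20.

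Finally, blocks are not free. In an open trial, staff see each allocation and may guess the end of a block. Varied, undisclosed sizes reduce this without removing it, so simple randomisation is a defensible trade-off. The planned multiple linear regression could also carry a hospital term, and its covariates may be listed in an analysis plan not shown here.

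**Conclusion.** The point holds, and it is modest. Under either reading of the two lists, the method does not secure the within-hospital balance that stratifying is meant to give. Its size depends on the reading: large under true simple randomisation (54% for at least one hospital of 35 at 22:13 or worse), small at that site size under 25/25 lists (about 5%), and still visible there at a site of 20 (15%).

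The consequence is a less tidy comparison and about one point of power at the 95th percentile of overall imbalance. It is not a biased test. A reader should not take it that no list will be finished, since two sites could reach 50.

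The conclusion rests on the Randomization section being the operative description of allocation, on a two-sided 5% t-test, and, for the 54% and 5%, on equal recruitment of 35 per hospital.

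**What to change.** Generate each hospital's sequence as permuted blocks of randomly varied size (for example 4 and 6), keep the sizes undisclosed to the sites, and fill the same 50 numbered envelopes from it. If recruitment has begun, change unopened envelopes only. Reword the Randomization section to name the block method in place of simple random sampling, leaving the block sizes to a document that the sites do not see.

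Include hospital as a factor in the primary PAM regression, so that the analysis reflects the stratification.

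The cost is regenerating four lists and refilling envelopes, with no more patients, plus the somewhat greater predictability of blocks in an open trial. If the envelopes cannot be changed, the hospital term alone handles most of any imbalance between hospitals.

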### Ethical aspects

The present study has been approved by the Clinical Research Ethics Committee (CREC) of the Fundación Alcorcón Hospital and it will also be approved by the CREC of each research center. Both the staff involved in the project and researchers know and vow to respect local and international regulations for human experimentation, including the Helsinki declaration and its revisions, the Belmont report and other related documents.

Data confidentiality will respect the Law on Data Protection (Organic Law 5/92 of October 29 on the regulation of the automated processing of personal data, BOE October 30, 1992 modified by the Organic Law 15/1999, of December 13, Protection of Personal Data and Law 41/2002, of November 14).

Patients will be informed in detail about the protocol and will sign a written informed consent before being included in the study.

### Limitations of the study

Even if the ACP program intervention is homogeneous in both groups, and everyday clinical practice is very similar in all centers, the organization of each HF Unit can vary. Despite this fact, this scenario parallels real clinical variability. Even though clinical management will be similar in both groups, as an open clinical trial there is a risk of expectation and attention bias. This might make it difficult to ensure that researchers' higher engagement with patients in the intervention group will not skew results. Finally, the study is restricted to patients with advanced HF, and therefore its conclusions and extrapolation to other advanced chronic pathologies is limited.

## Discussion

An ACP program involves planning decisions for patients who are at risk of losing the ability to decide. To do this, patients have to be adequately informed and supported by the healthcare team, so that they can establish their preferences regarding health. Possible future clinical scenarios must be foreseen so that the patients can express their wishes.

All these possible scenarios and the patient’s values must be known by their healthcare team and entered into their medical record, so as to ensure the patients’ wishes are respected if there is a situation in which they are unable to express their care preferences.

The characteristics of patients with advanced HF make them a model for designing ACP programs, given the high prevalence of this disease, the progressive increase in its incidence and it’s clinical characteristics: a low life expectancy in advanced phases and the ability to foresee future clinical scenarios on which is possible to plan decision-making [21]. Until now, the efficacy of this type of program has not been measured, so this Clinical Trial can provide relevant data for future ACP projects.

## Data Availability

Not applicable (no data or study results yet available).

## Abbreviations

ACP: Advanced Care Planning
HF: Heart failure.
AD: Advance directives
ACCF/AHA: American College of Cardiology Foundation/American Heart Association
PAM: Patient activation measure
SD: Standard deviation
